## Abstract

**Background:**

In New Zealand, around 45,000 people live with stroke and many studies have reported that benefits gained during initial rehabilitation are not sustained. Evidence indicates that participation in physical interventions can prevent the functional decline that frequently occurs after discharge from acute care facilities. However, on-going stroke services provision following discharge from acute care is often related to non-medical factors such as availability of resources and geographical location. Currently most people receive no treatment beyond three months post stroke. The study aims to determine if the Augmented Community Telerehabilitation Intervention (ACTIV) results in better physical function for people with stroke than usual care, as measured by the Stroke Impact Scale, physical subcomponent.

**Methods/design:**

This study will use a multi-site, two-arm, assessor blinded, parallel randomised controlled trial design. People will be eligible if they have had their first ever stroke, are over 20 and have some physical impairment in either arm or leg, or both. Following discharge from formal physiotherapy services (inpatient, outpatient or community), participants will be randomised into ACTIV or usual care. ACTIV uses readily available technology, telephone and mobile phones, combined with face-to-face visits from a physiotherapist over a six-month period, to help people with stroke resume activities they enjoyed before the stroke. The impact of stroke on physical function and quality of life will be assessed, measures of cost will be collected and a discrete choice survey will be used to measure preferences for rehabilitation options. These outcomes will be collected at baseline, six months and 12 months. In-depth interviews will be used to explore the experiences of people participating in the intervention arm of the study.

**Discussion:**

The lack of on-going rehabilitation for people with stroke diminishes the chance of their best possible outcome and may contribute to a functional decline following discharge from formal rehabilitation. Best practice guidelines recommend a prolonged period of rehabilitation, however this is expensive and therefore not undertaken in most publicly funded centres. An effective, cost-effective, and preference-sensitive therapy using basic technology to assist programme delivery may improve patient autonomy as they leave formal rehabilitation and return home.

**Trial registration:**

ACTRN12612000464864

## Background

Stroke is the leading cause of disability in ageing populations of developed countries [1]. In New Zealand around 45,000 people live with stroke and only 30% are independent in activities of daily living [2,3]. International figures indicate that only 40% of people with stroke achieve even minimal levels of physical activity [4]. A low level of physical activity over time leads to a gradual physical deterioration and loss of function, which has a detrimental impact on participation and quality of life (QoL) [5,6]. People with stroke are more likely to have a significantly reduced QoL than an age-matched population [7], to the extent that in an Australian study, 8% of people with stroke rated their quality of life as equal to or worse than death [8]. A recent meta-analysis of physiotherapy interventions in chronic stroke pooled the results from 15 trials of community-based physiotherapy and reported a favourable effect on mobility-based measures; a meta-analysis of primary mobility-based outcomes showed a significant effect of the intervention (effect size 0.29, 95% CI 0.14, 0.45) [9]. Participants with stroke in a qualitative study found telerehabilitation to have a broader range of benefits than anticipated by the researchers. Participants expressed perceived increased autonomy and appreciated the flexible and self-directed nature of telerehabilitation. The therapist’s role changed over time from a directive approach to a more motivational and facilitatory one [10]. There is evidence that even low intensity activity-based interventions improve independence in community-dwelling adults who have had a stroke and can positively influence QoL [11-13]. It appears that ongoing participation in physical activity prevents the decline in functional independence commonly seen in people with stroke once their rehabilitation has ceased. National and international stroke best-practice guidelines reflect this, and recommend long term engagement in some form of physical activity after discharge from hospital [14-16]. A Cochrane review showed that people with stroke who received long-term rehabilitation (up to one year post-stroke) had increased odds of a positive outcome and were more likely to be independent in functional tasks [11]. Despite this, in New Zealand many people with stroke do not receive any physiotherapy beyond three months post-stroke [17]. The benefits gained during initial rehabilitation are often not sustained in the long term, as people reduce activity levels and cease engagement in exercise programmes, leading to functional deterioration [18]. A consequence of this functional deterioration is high rates of admission to hospital and residential care within the first 12 months post-discharge [19]. Healthcare resources are limited, and whether an individual receives appropriate and on-going stroke services is often related to non-stroke factors, such as resource availability, geographical location, age, and personal finances [20,21]. Patients are frequently told they are discharged from therapy because they have reached a plateau, when the decision to discharge is likely to be more complex and includes consideration of resource availability [9,22]. People with stroke are often disappointed when they are discharged from rehabilitation; their disappointment is related to unmet expectations of recovery and a desire to receive rehabilitation until they perceive it is no longer needed [21,23]. Although the New Zealand Best Practice Guidelines recommend long-term rehabilitation, there are questions about feasibility [24] and the cost of ongoing rehabilitation. Our aim is to deliver an intervention that increases self-directed activity with a return of the locus of control to the person with stroke, utilising telerehabilitation to reduce the cost of rehabilitation. Technologies available for telerehabilitation delivery range from telephones and mobile phones, which are available in the majority of homes, through to more expensive internet-based solutions, virtual reality and robotic systems. In a review of home-based physical activity interventions for older adults, four of seven studies used telephone communication to encourage continued participation, with encouraging results. There were high levels of participation over the short and long term (86% to 93% and 44% to 68% of people adhering to their exercise programme respectively) [25]. It has been suggested that physiotherapists are ideally placed to assist people with stroke transition from hospital to home [26] but there has been considerable international professional resistance to using a telerehabilitation-based service, with a view that the loss of hands-on treatment may lead to poorer outcomes [27]. However, evidence from studies in various chronic health conditions show that telerehabilitation approaches can be successful in improving outcomes [28-30]. The American Physical Therapy Association is revising its stance to support telerehabilitation as a delivery method [31]. One feasible approach to telerehabilitation in New Zealand may be to provide limited home visits by a physiotherapist, a structure that has been used successfully by the Otago Exercise Programme (OEP) for falls prevention [32]. The OEP programme provided a limited number of home visits supplemented by telephone calls [33,34]. For ACTIV to be adopted by Regional Health Services, there must be clear evidence that it produces a significant improvement to people’s outcomes after stroke in a cost-effective manner. Telerehabilitation is a relatively new mode of delivery of interventions [35], with limited evidence concerning the net costs, the effectiveness and the cost-effectiveness compared with standard care. The current study will be among the first to assess the benefits and costs of an intervention that uses telerehabilitation as part of the package.

## Methods/design

### Study aims

The overarching aim of this study is to investigate ACTIV for people with stroke to improve the transition from hospital to community living. The specific aims are to:

1. Determine the effect of ACTIV on physical function

Primary research question: At the end of the 6-month intervention, will ACTIV improve physical function in people with stroke compared to a usual care control group, as measured by the physical subcomponent of the Stroke Impact Scale (SIS 3.0)?

Secondary research question 1: At the 12-month follow-up, will any physical gains achieved by the intervention group at the end of the intervention be maintained as measured by the physical subcomponent of the SIS 3.0?

Secondary research question 2: At the end of the 6-month intervention and at follow-up, will ACTIV improve physical function in people with stroke, compared to a usual care control group as measured by the physical performance measures and the stroke self-efficacy questionnaire?

2. Determine the effect of ACTIV on health outcomes and quality of life.

Secondary research question 3: Over the study period, will ACTIV improve health outcomes and quality of life in people with stroke compared to a usual care control group as measured by the SIS 3.0?

3. Determine the effect of ACTIV on hospital and residential care admission rates.

Secondary research question 4: Over the study period, will participation in ACTIV result in a reduction in hospital admissions compared to the usual care control group?

4. Determine the cost and cost-effectiveness of ACTIV.

Secondary research question 5: Over the study period, will ACTIV be cost-effective compared to usual care in reducing aspects of the burden of care in people with stroke?

5. Explore participant experience of and satisfaction with ACTIV.

Qualitative question: What are the experiences, in particular, the perceived benefits and challenges for participants in ACTIV?

### Study design

This is a multi-site, two-arm, assessor blinded, parallel randomised controlled trial (RCT). Alongside the RCT, an economic evaluation will compare the cost-effectiveness of the intervention with usual care and preferences for stroke rehabilitation delivery, in addition, a qualitative component will explore the experiences of participants with the intervention. Enrolment will occur in New Zealand in the North Island at Middlemore Hospital (South Auckland), North Shore Hospital (North Auckland), and in the South Island at The Princess Margaret Hospital (Christchurch), and Dunedin Hospital (Dunedin). People will be eligible for inclusion in the study at the time of discharge from standard physiotherapy. Standard physiotherapy will include inpatient rehabilitation in general medical or specialist stroke care facilities, and outpatient or community physiotherapy post-discharge from hospital. Outcome assessments will be conducted at baseline, immediately after the six-month intervention and at six months post-intervention by an assessor blinded to group allocation. Figure 1 outlines the study design and procedure.

**Figure 1 F1:**
[figure not shown]
Design and procedure of study.

### Ethical approval

The New Zealand Multi-regional Ethics Committee gave ethical approval for this study (MEC 11/11/089) and each of the centres where recruitment is to take place approved the study. Māori consultation was undertaken in each centre to ensure cultural values that may differ between *Iwi* (tribe) were given appropriate consideration. All participants will give written informed consent prior to participating in the study.

### Study sample

#### Sample size

Sample size computations are based on a 5% per comparison significance level and a two-tailed critical region. Due to the variation in response to physiotherapy intervention after stroke a conservative approach has been taken with the assumption that there will be no correlation between baseline measures and final outcome. Two previous studies [36,37] have indicated consistent baseline SDs for the physical function subcomponent of the SIS, for a pooled baseline SD of approximately 21.7. A naïve combination of the clinically important differences (CID) from Lin and colleagues in 2010 [36], based on a geometric mean of the elements, yields a CID for the SIS physical function subcomponent score of 5.3, corresponding to an effect size of about 0.25. In their rehabilitation study, Marsden and colleagues 2010 [37] obtained standard errors for the mean differences in measurement, of 9.5 and 6.6 for their control and treatment groups, respectively. Using these values, 38.4 participants per arm will be required to detect the target effect size with 80% power, based on the appropriate *t*-distribution for the difference of two such changes from baseline. A total sample size of 96 will be required, allowing for an attrition rate of 20% over the 12-month research period. With these numbers, the probability is approximately 80% that the study will detect a treatment difference, if the true difference between the changes in ACTIV and usual care control group is at least 5.4 points in the physical subcomponent of the SIS3.0.

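### The sample size inputs and the stated 80% power cannot all hold: 38.4 per arm needs a baseline-outcome correlation of about 0.93, while the text assumes none and calls that conservative

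*Protocol article*

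**What the plan says.** All the inputs stand in one paragraph of the Protocol article, under Sample size.

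- Test: "Sample size computations are based on a 5% per comparison significance level and a two-tailed critical region".
- Correlation: "a conservative approach has been taken with the assumption that there will be no correlation between baseline measures and final outcome".
- Spread of the score: two earlier studies are combined "for a pooled baseline SD of approximately 21.7".
- Target: combining published clinically important differences (CIDs) "yields a CID for the SIS physical function subcomponent score of 5.3, corresponding to an effect size of about 0.25".
- Spread of change: an earlier rehabilitation study "obtained standard errors for the mean differences in measurement, of 9.5 and 6.6 for their control and treatment groups, respectively".
- Result: from these values, "38.4 participants per arm will be required to detect the target effect size with 80% power", based on a t-distribution for the difference between two changes from baseline. Allowing for 20% attrition gives 96 in total.
- Power statement: about 80% "if the true difference between the changes in ACTIV and usual care control group is at least 5.4 points".

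The Quantitative analysis section plans an ANCOVA of the 6-month change, adjusted for baseline, with site as a random effect.

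**The concern.** With a score SD of 21.7 and no correlation between baseline and follow-up, changes from baseline vary more than the scores themselves, and adjusting for baseline gains nothing. A 5-point difference is then hard to see with fewer than 40 per arm. Yet the paragraph reports 80% power, so some of its inputs cannot have been used.

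This is the article's only power justification for the primary outcome. A reader told that the trial has 80% power at the CID on a cautious assumption would give a non-significant result more weight than it deserves if the true correlation is well below the value the calculation needs.

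**Working it through.** **1. Reproduce the plan's figure.** Enter 9.5 and 6.6 as SDs of individual change, with two-sided 5%, 80% power and a 5.3-point difference.

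- Sum of variances: 9.5² + 6.6² = 90.25 + 43.56 = 133.81. Root mean square SD = √(133.81/2) = 8.18.
- Normal approximation: n = 133.81 × (1.960 + 0.8416)² / 5.3² = 133.81 × 7.849 / 28.09 = 37.4 per arm.
- Noncentral t with pooled variance: n = 38.37 per arm, against the stated 38.4.
- Attrition: 2 × 38.4 / 0.80 = 96, as stated.

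The figure is recovered without using 21.7 or any correlation.

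**2. The correlation this implies.** With SD 21.7 at both times (an assumption; the article gives a baseline SD only):

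- Change scores: SD² = 2 × 21.7² × (1 − ρ), so ρ = 1 − 66.9/941.8 = 0.929.
- ANCOVA residual: SD² = 21.7² × (1 − ρ²), so ρ = √(1 − 66.9/470.9) = 0.926.

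The contradiction does not depend on equal SDs. At ρ = 0 the variance of change is the baseline variance plus the follow-up variance, so the change SD cannot be below 21.7 whatever the follow-up SD. Both 9.5 and 6.6 are far below it.

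**3. Power under the stated assumptions.** With 38.4 per arm, the standard error of the difference is SD × √(2/38.4) = 0.2282 × SD, on 74.8 degrees of freedom. Site effects are ignored.

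- ANCOVA, ρ = 0: SD 21.7, standard error 4.95, noncentrality 5.4/4.95 = 1.09, power 19.0%.
- Change scores, ρ = 0: SD 21.7 × √2 = 30.7, standard error 7.00, noncentrality 0.77, power 11.9%.
- 80% power needs a noncentrality of about 2.84, so the detectable difference is 2.84 × 0.2282 × SD = 0.648 × SD: 14.1 points for ANCOVA and 19.9 for change scores.

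**4. Planned ANCOVA over assumed correlations** (38.4 per arm; power at 5.4 points):

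| ρ | Residual SD | Power | 80%-detectable difference |
|---|---|---|---|
| 0 | 21.7 | 19% | 14.1 |
| 0.5 | 18.8 | 24% | 12.2 |
| 0.8 | 13.0 | 43% | 8.4 |
| 0.9 | 9.5 | 69% | 6.1 |
| 0.93 | 8.0 | 83% | 5.2 |

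**5. If 9.5 and 6.6 are true standard errors of group mean change.** Each must be multiplied by the square root of its source group size, which the article does not give. Assuming 10 per group, the SDs are 30.0 and 20.9 and power at 5.4 points is 14.7%. Assuming 20 per group, they are 42.5 and 29.5 and power is 9.8%.

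**The case against.** The strongest defence is that the arithmetic is right for the method named. If 9.5 and 6.6 are SDs of change that were merely mislabelled, 38.4 per arm does give 80% power at 5.3 points. That stands. A reader might infer that the trial's true power is 12% to 19%, or that the labelling slip produces those figures. The article supports neither. The 12% to 19% comes from taking SD 21.7 and zero correlation literally. The label is a separate question with its own range, and the article cannot settle it.

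A second defence is that final outcome means the change score. Baseline would then be unrelated to change, ANCOVA would gain nothing over a t-test on change, and conservative would be a fair word. This fits the calculation but not the sentence, which speaks of the final outcome. It would also still imply a correlation between baseline and final score of 21.7/√(21.7² + 8.18²) = 0.94.

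Third, the Primary outcome section cites a test-retest ICC of 0.98, so a high correlation is not absurd and zero is an extreme case. That is fair as far as it goes. However, short-term reliability is not a six-month correlation, and the paragraph itself gives variable response to physiotherapy as its reason for assuming none.

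Two further inferences should be resisted. An effect size of 0.25 does not by itself rule out 80% power with 38 per arm: it is scaled to the baseline SD, and on the change scale the same target is 5.3/8.18 = 0.65. The use of both 5.3 and 5.4 points is also immaterial, since power at 38.4 per arm is 80.0% and 81.5% respectively.

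**Conclusion.** The paragraph is wrong as written: its inputs and its stated power are incompatible. The calculation behind 38.4 per arm uses a change SD of 8.18, which needs a correlation of about 0.93 if the SD is 21.7 at both times. The zero-correlation assumption was not applied, and the calculation is the opposite of conservative in that respect. This holds whether 9.5 and 6.6 are SDs or standard errors.

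What the trial's power actually is cannot be read from the article. It is about 80% if the two figures are SDs of change and a correlation near 0.93 is realised. It is about 19% (ANCOVA) or 12% (change scores) if the stated SD and zero correlation are taken at face value. It is about 15% to 10% if the figures are standard errors from groups of an assumed 10 to 20.

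**What to change.** Rewrite the Sample size paragraph, with no change in enrolment.

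1. Check in the source study whether 9.5 and 6.6 are SDs of change or standard errors. Correct the label, or convert them with the source group sizes.
2. Delete the statement of zero correlation and the description of the approach as conservative. State the change SD and the baseline-outcome correlation actually assumed.
3. Restate the power and detectable difference of the planned ANCOVA for 96 participants under that assumption, and over a plausible range of lower correlations, as in the table above.

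The cost is one check of the source and some rewording. The drawback is that the stated power will look less favourable.

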#### Recruitment

Participants will be recruited via hospital-based stroke and rehabilitation services. In all four hospitals, potential participants will be identified via the Community-Based Rehabilitation Team or Community Stroke Rehabilitation Team. In addition, discharges from acute medical wards and rehabilitation wards will be checked for people discharged directly from these services. To access people with stroke who are under 65 years of age, in the Christchurch area, discharges from Burwood Brain Injury Service will be checked. Eligible participants will be mailed an information sheet and letter of introduction to the project; this will be followed up with a telephone call to ascertain interest. Potential participants who identify as Māori or who express a need for more information will be given the opportunity for a face-to-face discussion of the information sheet. For those interested in participation, telephone screening will be undertaken with the potential participant or their spouse/carer once they have been discharged from hospital care, to establish eligibility. If they meet selection criteria an assessor will make an appointment for the baseline assessment to be carried out. All assessments will take place in the participant’s home.

### Inclusion criteria

People will be eligible for inclusion if they have had a first ever hemispheric stroke of haemorrhagic or ischaemic origin; are over the age of 20 years; have been discharged from inpatient, outpatient and community physiotherapy services to live in their own home (participants involved in other forms of therapy such as Occupational Therapy, Tai Chi or community exercise programmes will not be excluded); have medical clearance from their General Practitioner to participate in a low to moderate level activity programme; score at least 3 on a telephone cognitive screening questionnaire [38]; have a limitation in physical function of leg, arm or both.

Limitation in physical function of the leg will be established if patients have a score between 4 and 6 on the Functional Ambulation Category (FAC) [39] and in the case where they score 6, also answer ‘No’ to at least one of the two walking parameter questions below:

1. Can you get across the road at the traffic lights, in the time the green man is showing?

2. Are you able to walk 400m? (that is, ¼ mile, one to two blocks)

Limitation in physical function of the arm will be established using the questions below, if they answer ‘Yes’ to at least one question in section A and ‘No’ to at least one question in section B.

A. With your affected arm are you able to:

1. Switch on a light?

2. Bring a glass of water to your mouth?

3. Move your fingers and thumb independently?

B. Are you able to:

1. Use a keyboard equally with both hands?

2. Holding a pencil with your affected hand make rapid dots on a piece of paper?

3. Take a spoonful of liquid to your mouth without spilling it or bending your neck?

